### 9.6. HEALING PROCEDURE IN THE CONTROL GROUP

Patients assigned to the control group will receive the same treatment, except for the application of the sheet of expanded ADSCs in a biological fibrin-hyaluronic acid matrix. In this case, the non-adhesive polyurethane foam appliance (New Cutimed® Siltec Plus 73288/001) will not be considered secondary. They will also receive Jobst® Compri2® 40mmHg compression therapy.

## 10. EVALUATION OF THE RESPONSE

### 10.1. MAIN VARIABLE

#### Feasibility

Defined as the possibility of completing the administration of the 4 doses of the investigational drug in at least 80% of patients randomized to the treatment group

#### Safety:

Incidence of AE, SAE, AR, as well as SUAR, throughout the intervention period, as well as the 12 months after the end of treatment

### 10.2. SECONDARY VARIABLES

Effectiveness:

The answer will be analysed through clinical and biological parameters

Clinical variables:

- Percentage of patients who achieve complete healing at 12 weeks of follow-up (complete epithelialization maintained for 2 weeks) when comparing control group versus treatment.
- Time elapsed (days) to wound closure, measured from the start of treatment to the absence of continuity solution (when the wound bed is completely re-epithelialized and with new tissue) when comparing control group versus treatment.
- Percentage of patients who presented better in the total score and by Resvech 2.0 scale (size of injury, depth of affected tissues, borders, type of tissue in the wound bed, exudate, and infection · inflammation) with respect to baseline and when comparing control group versus treatment.
- Percentage reduction in wound extension (relative area, measure, graded rule) with respect to baseline visit and when comparing the control group versus the experimental group.
- Percentage of patients who have a decrease in the score of the AVS pain scale with respect to the baseline visit when comparing the control group versus the experimental group.
- Percentage of patients who perceive better quality of life according to the score obtained in the CIVIQ20 throughout the treatment/follow-up with respect to the baseline visit and when comparing both groups.

Biological variables:

- Evolution of the pattern of cytokines and growth factors obtained from ulcer exudate samples at day 0, +7, +14, +21 and +28 when comparing both groups and their relationship with ulcer healing.

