### 5.3. SAMPLE SIZE

Twenty patients with VUs, who meet all inclusion criteria and none exclusion criteria, will be included and will be randomized 1:1 to two intervention arms: experimental and control (10 patients treatment group/10 patients control group).

The 10 patients in the experimental arm will receive 4 doses of the investigational drug: adult mesenchymal stem cells from adipose tissue expanded in the biological matrix of fibrin-hyaluronic acid on the base or wound bed, while the 10 patients in the control group will be treated with conventional therapy.

This is a phase I/II clinical trial, proof of concept, of which there are no previous studies, so no mathematical calculation of the sample size has been carried out.

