### 6.3. INCLUSION CRITERIA

To be eligible for inclusion in the study, patients must meet all the inclusion criteria described below:

1. Signing the informed consent (IC) after reading the patient information sheet (HIP).
2. Over 18 years of age of both sexes.
3. Active or recurrent venous ulcer (C6 according to the CEAC clinical classification, Annex 5) in the lower extremity with an area of between 5-10 cm^2.
4. Grade III on the Widmer scale.
5. Distal pulses in palpable lower limbs (tibial and pedium). ABI between 0.8 - 1.3.

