## 8. TREATMENT ASSIGNMENT

### 8.1. RANDOMIZATION

The method of randomization is simple, without restrictions, for it a table of random numbers. The randomization list will be kept and managed by the Coordination Unit of the promoter, which will be the one who will assign the treatment after confirming compliance with the selection criteria.

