## 11. STATISTICAL ANALYSIS

The statistical analysis will be carried out by an independent biostatistician under the supervision of the project's Principal Investigator. All continuous variables will be described using standardized statistical measurements. The categorical variables will be summarized in frequency tables. For descriptive analyses, absolute or relative frequencies will be used in the case of relative variables. The

quantitative variables, depending on whether they follow a normal distribution (Saphiro-Wilk ( $n < 50$ )), will be shown as  $m \pm SD$  (mean and standard deviation) and range (minimum and maximum) or P50 [P25-P75]

(median, interquartile range). To compare the different variables in the two groups, the Pearson Chi-square test or the exact Fisher test will be applied in the case of qualitative variables, while , for quantitative variables, the ANOVA and post hoc tests or the Kruskal-Wallis H and Mann-Whitney U tests will be used, always applying the Bonferroni correction ( $\alpha/\text{number of possible comparisons}$ ). Values with  $p < 0.05$  will be considered statistically significant.

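### Section 11 fixes tests without covariates for area reduction and time to closure; pre-specifying starting ulcer area would guard the single realised estimate against chance imbalance in size

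*Protocol*

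**What the plan says.** Section 10.2 lists two secondary efficacy variables that bear on this point. One is the "Percentage reduction in wound extension (relative area, measure, graded rule) with respect to baseline visit", compared between the groups. The other is "Time elapsed (days) to wound closure, measured from the start of treatment to the absence of continuity solution", also compared between the groups. The first is scaled to the patient's own starting area; the second is not scaled.

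Inclusion criterion 3 (section 6.3) admits a venous ulcer "in the lower extremity with an area of between 5-10 cm"², a twofold range. Section 8.1 states: "The method of randomization is simple, without restrictions". Nothing stratifies or balances on ulcer size.

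Section 11 gives the tests that will be used "To compare the different variables in the two groups". For quantitative variables these are ANOVA with post hoc tests, or Kruskal-Wallis and Mann-Whitney. No covariate is named. Length and width are recorded at visit 1 and again at visit 2 (day 0), as section 7 sets out, so starting area is available for every treated patient.

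**The concern.** Dividing by baseline removes the scale of the measurement but not necessarily its dependence on starting size. If an ulcer closes by its edge moving inwards, the same edge movement removes a larger share of a small ulcer than of a large one. Days to closure has no baseline scaling at all, so a larger ulcer simply has further to go.

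With some 10 patients per arm, the arms can differ in mean starting area by chance. Part of the observed difference in area reduction or closure time would then reflect size rather than treatment, and the tests named in section 11 cannot separate the two. If no covariate is fixed in advance and the arms turn out to differ, the choice between adjusted and unadjusted results would be made after seeing the data. These two variables will supply much of the trial's proof-of-concept evidence on efficacy.

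**Working it through.** The plan has no figure of its own to reproduce: section 5.3 states that "no mathematical calculation of the sample size has been carried out".

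**Inputs from the protocol**
- Starting area 5 to 10 cm² (section 6.3).
- 20 patients, planned as 10 per arm (section 5.3).
- Area recorded as length × width (section 9.5, Annexes 2 and 4).

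**Assumptions, not in the protocol**
- Circular ulcers with the same edge advance *m* in every ulcer.
- Starting area uniform over 5 to 10 cm².

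**Step 1. Dependence of the outcomes on starting size.** For a circular ulcer, length × width = (2R)², so R = √A / 2.
- A = 5 gives R = 1.12 cm; A = 10 gives R = 1.58 cm.
- Percentage reduction = 1 − (1 − m/R)².

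| m (cm) | 5 cm² ulcer | 10 cm² ulcer | gap (points) |
|---|---|---|---|
| 0.25 | 39.7% | 29.1% | 10.6 |
| 0.4 | 58.8% | 44.2% | 14.6 |
| 0.5 | 69.4% | 53.2% | 16.2 |
| 0.75 | 89.2% | 72.4% | 16.8 |

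At a constant edge speed, time to closure is proportional to R, so the ratio is √(10/5) = 1.41 whatever the speed.

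**Step 2. How often the arms differ in size.**
- SD of area = 5/√12 = 1.44 cm².
- SE of the difference in means with 10 per arm = 1.44 × √(2/10) = 0.645 cm².
- P(|difference| > 1 cm²) = P(|Z| > 1/0.645 = 1.55) = 12%. For 1.5 cm² it is about 2%.
- Simple randomization also lets the arm sizes vary, which raises the 12% to about 13% in simulation.

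**Step 3. What a 1 cm² difference does.** Take arm means of 7 and 8 cm² with m = 0.4.
- Reductions are 51.3% and 48.6%, a shift of 2.7 points. For m of 0.25 to 0.75 the shift is 2.0 to 3.3 points.
- Closure time ratio = √(8/7) = 1.07, or 7%.

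**Step 4. Validity and precision, by simulation under the same kind of model with 10 per arm.**
- With no treatment effect, the mean arm difference was 0.0 to 0.2 points and the Mann-Whitney type I error was 0.04 to 0.05.
- The chance SD of the unadjusted arm difference was about 4 to 10 points, depending on between-patient variation.
- Adjustment lowered that SD from 4.3 to 3.9 points when size explained much of the outcome (r about −0.43). It gave no gain when other variation dominated (9.6 against 9.7, and 7.7 against 7.8).
- Power changed by about +5, +2, +1 and −1 points for a between-patient SD of log healing speed of 0.2, 0.3, 0.4 and 0.6.

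**The case against.** The strongest objection is that nothing here is wrong. A comparison of randomized arms needs no covariate to be valid, and Step 4 confirms this: no bias on average, and type I error at its nominal level. A reader might infer from the size dependence that the planned comparison is biased, or from the unrestricted randomization that the arms will be unequal. The documents support neither. Balance is not enforced, which is different from being absent, and size dependence in one patient does not bias the arms on average. Nor do the figures support a large gain in power.

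Three further objections carry weight. The healing geometry is an assumption that the protocol neither states nor supports. The entry window already limits variation in size, and section 1.17 sets up a committee to check it. Both variables are secondary in a 20-patient trial whose main variables are feasibility and safety.

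It can also be said that covariates belong in the statistical analysis plan, which is not shown. This carries less weight. Section 11 does not defer the choice; it says which tests will be used, so an adjusted analysis would have to depart from that text or add to it. Finally, the whole entry range falls in one RESVECH size category (4 to 16 cm², Annex 6). That does not answer the point, because percentage area and days are continuous.

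**Conclusion.** The point stands as a minor improvement. As written, neither outcome is adjusted for a starting value that may vary twofold, is not balanced by design and is already collected. The risk is a chance difference in the one trial that will be run. In about 12% of trials the arms would differ by more than 1 cm² in mean area, and a 1 cm² difference moves area reduction by about 2 to 3 points and closure time by about 7%. Against a chance SD of about 4 to 10 points for the difference in area reduction, that shift is small. The expected precision gain is small too and may be nil.

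The case is stronger for time to closure, which has no baseline scaling. All sizes rest on circular ulcers, equal edge advance and uniform starting areas. The main benefit is that the analysis is fixed before any imbalance is seen.

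**What to change.** In section 11, pre-specify log baseline area, measured on day 0, as the single covariate:

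- **Percentage area reduction:** analysis of covariance with arm and log baseline area. Use a rank-based version if the data are non-normal or many ulcers reach 100%, since the outcome is capped there.
- **Time to closure:** Cox model with arm and log baseline area, with unhealed ulcers censored at their last assessment.
- **Sensitivity analysis:** the unadjusted comparison that section 11 now names.

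No new data are needed. The cost is a short addition to section 11, one degree of freedom with 20 patients, and a slight loss of precision if baseline area proves unrelated to outcome.

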#### 4.2. SECONDARY OBJECTIVES

1. To determine the effect of experimental treatment on wound closure time compared to the control group.
2. To assess the effect of the experimental treatment on the scar evolution of the injury, considering depth, dimensions, type of edges, tissue and exudate compared to the control group.
3. To assess the effect of the experimental treatment on the concentration of growth factors closely related to wound healing (cytokines IL-6, IL-4, TGF- $\beta$ 1 and IL-10) on the exudate of injury at day 0, +7, +14, +21 and +28 compared to the control group and its possible relationship with the rest of the efficacy parameters.

4. To evaluate the evolution of pain derived from the presence of UVs in the group treated with the ADSCs, compared to the control group.
5. To determine the perceived quality of life after treatment with the experimental treatment compared to the control group.

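### Pain, quality of life and RESVECH are reduced to any-improvement percentages, which costs much of the precision available with 10 patients per arm

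*Protocol*

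**What the plan says.** Protocol Section 10.2 defines three clinical variables as counts of improved patients:

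- Pain: "Percentage of patients who have a decrease in the score of the AVS pain scale with respect to the baseline visit".
- Quality of life, again counted as a percentage of each arm: "perceive better quality of life according to the score obtained in the CIVIQ20 throughout the treatment/follow-up with respect to the baseline visit".
- Wound scale: "Percentage of patients who presented better in the total score and by Resvech 2.0 scale".

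None of them requires an improvement of any particular size. The same list keeps wound area quantitative: "Percentage reduction in wound extension (relative area, measure, graded rule) with respect to baseline visit".

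For comparing the arms, Section 11 says that "the Pearson Chi-square test or the exact Fisher test will be applied in the case of qualitative variables". For quantitative variables it names ANOVA with post hoc tests, or Kruskal-Wallis and Mann-Whitney. It names no method with baseline as a covariate. It adds a Bonferroni correction without fixing the number of comparisons.

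Section 4.2 puts the pain objective in terms of course over time: "To evaluate the evolution of pain derived from the presence of UVs in the group treated with the ADSCs", compared with control. Section 5.3 sets the arms at "10 patients treatment group/10 patients control group" and says that no sample size was calculated.

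**The concern.** A yes/no count of any improvement treats a one-point fall in pain and a complete resolution as the same result. Controls receive the same cleaning, debridement, foam dressing and compression (Section 9.6, Annex 4), so it is plausible that a good share of them will also improve a little. If they do, both percentages move towards 100% and the contrast between arms shrinks, even where the treated patients improve much more.

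With 20 patients there is little room for that loss. At stake are the pain, quality-of-life and RESVECH comparisons, and the effect estimates that a proof-of-concept trial should hand to the next one. The defect sits in the variable definitions, which belong to the protocol. An analysis plan that followed Section 10.2 would inherit it.

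**Working it through.** The protocol gives no power, effect size, SD or improvement rate, so there is no figure to reproduce.

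**Inputs from the protocol:** 10 per arm (Section 5.3); any-improvement variables (Section 10.2); chi-square or Fisher and p<0.05 (Section 11).

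**Assumptions, not in the protocol:** normally distributed scores; two-sided test; no Bonferroni correction, since the number of comparisons is not fixed; baseline-to-follow-up correlation r of 0.3 to 0.7; true effect of 1 SD of change in the central case.

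**1. The limit of Fisher's test at 10 against 10.** This step needs no assumption about rates or effects. Let all 10 treated patients improve.

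- 5/10 controls improve: 2 × C(10,5)/C(20,15) = 2 × 252/15504 = 0.0325.
- 6/10 controls improve: 2 × C(10,6)/C(20,16) = 2 × 210/4845 = 0.087.

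From 6 improved controls upward, no result in the treated arm can favour treatment at p<0.05. The probability of at least 6 improved controls out of 10 is 38%, 85% or 97% if the control improvement rate is 50%, 70% or 80%.

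The uncorrected Pearson chi-square is less strict. At 10/10 against 6/10 it gives 20 × (10×4 − 0×6)²/(10×10×16×4) = 5.0, p=0.025. At 10/10 against 7/10 it gives 20 × 30²/(10×10×17×3) = 3.53, p=0.060. However, at 10 against 6 the expected number of non-improvers is 4/2 = 2 per arm, which is where Fisher's test is normally preferred.

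**2. Power for a true effect of 1 SD of change.** If controls improve by m SD on average, the improvement rates are Φ(m) and Φ(m+1). Fisher power comes from enumerating all tables.

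| Control mean improvement | Rates, control vs treated | Fisher power |
|---|---|---|
| 0 SD | 50% vs 84% | 18.5% |
| 0.5 SD | 69% vs 93% | 8.8% |
| 1 SD | 84% vs 98% | 1.0% |

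The quantitative alternatives do not depend on m:

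- Change score, t-test with 18 df, noncentrality 1/√(2/10) = 2.24: power 56%.
- ANCOVA with r = 0.5: the variance relative to the change score is (1+r)/2 = 0.75, so the standardised effect is 1/√0.75 = 1.155. With 17 df the power is 68% (66% by simulation).

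Uncorrected chi-square power is 33%, 20% and 9% at control rates of 50%, 70% and 80%: higher than Fisher, but well below 56%.

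**3. Sample size equivalent.** For 80% power in the same case with r = 0.5, by the normal approximation, the dichotomy needs 29, 41 or 57 per arm at control rates of 50%, 70% or 80%. The change score needs 16 and ANCOVA 12.

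**4. Asymptotic efficiency of the dichotomy.** Against the change score it is φ(z_p)²/[p(1−p)] at improvement rate p. Against ANCOVA, multiply by (1+r)/2.

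| Improvement rate | vs change score | vs ANCOVA, r = 0.3 | vs ANCOVA, r = 0.7 |
|---|---|---|---|
| 50% | 0.64 | 0.41 | 0.54 |
| 70% | 0.58 | 0.37 | 0.49 |
| 80% | 0.49 | 0.32 | 0.42 |
| 90% | 0.34 | 0.22 | 0.29 |

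The information lost is therefore 36 to 66% against the change score and 46 to 78% against ANCOVA.

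**5. Wider range.** With effects of 0.8 to 1.5 SD of the raw score, r of 0.3 to 0.7 and control rates of 50 to 80%, power runs from 2 to 51% for Fisher, 30 to 98% for the change score and 42 to 99% for ANCOVA.

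**The case against.** The strongest reply is that these are secondary variables in a proof-of-concept trial whose main variables are feasibility and safety, that no power was claimed, and that covariate adjustment is usually left to the analysis plan. Section 11 also says that continuous variables will be described, so the scores themselves need not vanish from the report. Most of this stands, and it limits how serious the point is. It does not remove it, because the choice of an any-improvement percentage is made in Section 10.2 itself.

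Several stronger readings are tempting, and the protocol does not support them:

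- *Baseline is ignored.* It is not. Each of the three variables is defined relative to baseline. What is absent is baseline as a covariate in the comparison.
- *Section 11 offers only tests meant for three or more groups.* It also names Mann-Whitney, which suits two arms, and ANOVA with two groups is valid. The post hoc and Kruskal-Wallis wording is superfluous but has no shown effect on any result.
- *Most of the information is always lost.* Against the unadjusted change score the loss passes half only at improvement rates of about 80% or more; at 50% it is 36%.
- *A large benefit would almost certainly be missed.* If controls do not improve on average, Fisher power is 38% for an effect of 1.5 SD and 53% for 2 SD. That is low, but it is not certain failure, and the protocol gives no control rate.
- *Objectives 2, 4 and 5 cannot be answered.* A weak test is not an unanswerable question, and the wound dimensions in objective 2 remain quantitative.

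**Conclusion.** The point holds in limited form. Section 10.2 reduces VAS pain, CIVIQ-20 and RESVECH 2.0 to improvement percentages without a threshold, and the tests named for them do not adjust for baseline. The firmest result needs no outside assumption about rates or effects: at 10 per arm, six controls with any improvement are enough to put a benefit out of reach of Fisher's test.

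The size of the power loss is conditional. The contrast between 1 to 19% for Fisher and 56% or about 68% for the quantitative analyses rests on normal scores, an effect of 1 SD of change and, for ANCOVA, a correlation of 0.5. The Bonferroni correction would lower all of these figures. Only the three score comparisons are affected; wound area, feasibility and safety are untouched. It is worth correcting because the correction is cheap, not because a main conclusion depends on it.

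**What to change.** In Section 10.2, define the between-group comparison for VAS, CIVIQ-20 and RESVECH total as the quantitative score at one named visit, for example day 84 (visit 14), adjusted for the baseline value by ANCOVA. Report it as a mean difference with 95% CI, with a rank-based sensitivity analysis. State which visit supplies the baseline, since Section 7 records all three scores at both visit 1 and visit 2. Keep the any-improvement percentages as description.

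The cost is protocol wording. The scores are already collected and no extra visit or patient is needed. The downside is reliance on model assumptions with 20 patients, which the rank-based analysis is there to check. Day 84 and ANCOVA are a reasonable choice, not the only sound one; what matters is that the score stays quantitative, is adjusted for baseline, and is compared at a visit fixed in advance.

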## 11. STATISTICAL ANALYSIS

The statistical analysis will be carried out by an independent biostatistician under the supervision of the project's Principal Investigator. All continuous variables will be described using standardized statistical measurements. The categorical variables will be summarized in frequency tables. For descriptive analyses, absolute or relative frequencies will be used in the case of relative variables. The

quantitative variables, depending on whether they follow a normal distribution (Saphiro-Wilk ( $n < 50$ )), will be shown as  $m \pm SD$  (mean and standard deviation) and range (minimum and maximum) or P50 [P25-P75]

(median, interquartile range). To compare the different variables in the two groups, the Pearson Chi-square test or the exact Fisher test will be applied in the case of qualitative variables, while , for quantitative variables, the ANOVA and post hoc tests or the Kruskal-Wallis H and Mann-Whitney U tests will be used, always applying the Bonferroni correction ( $\alpha/\text{number of possible comparisons}$ ). Values with  $p < 0.05$  will be considered statistically significant.

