  - B) Wound extension by means of a graduated ruler, measuring the greatest vertical length (length) and the longest perpendicular length (width). Photographs will be taken with the ruler located on the injury to evaluate the evolution of the wound and the measurement of the perimeter.
6. Visual Analogic Pain Scale (VAS) (At visits 6, 7, 8, 9, 10, 11, 12, 13 and 14).
7. Sample collection for the exudate study (Annex 3) (Visit 6).
8. Assessment of quality of life using the CIVIQ 20 questionnaire (At visits 6, 7, 8, 9, 10, 11, 12, 13 and 14).
9. VU treatment (Annex 4).
10. It will be recorded in the medical record if there has been any concomitant change in your medication since the last visit.

11. It will be recorded in the clinical history if any adverse event or death has occurred since the last visit.

From visit 15 onwards, two types of visits may be carried out depending on the state of the ulcer under study:

- If the ulcer is not healed, a weekly safety and efficacy follow-up will be carried out until it is completely closed. The following information will be collected on these visits:
  1. Date of visit
  2. Evaluation of the ulcer:
    - A. Macroscopic observation of the injury: epithelialization tissue, presence of exudate and existence of bleeding, using the Resvech scale.
    - B. Wound extension by means of a graduated ruler, measuring the greatest vertical length (length) and the longest perpendicular length (width). Photographs will be taken with the ruler located on the injury to evaluate the evolution of the wound and the measurement of the perimeter.
  3. VU treatment (Annex 4).
  4. It will be recorded in the medical record if there has been any concomitant change in your medication since the last visit.
  5. It will be recorded in the clinical history if any adverse event or death has occurred since the last visit.

Once the ulcer is closed, a face-to-face visit will be made 15 days after closing to ensure the same, in which they will perform the same tests and collect the same information described above.

- If the ulcer is healed, a follow-up will be carried out every 15 days of security (face-to-face or telephone). This additional follow-up will focus on assessing the long-term safety of DMMCs by collecting adverse events and death events.

All patients should complete the 12-month follow-up period after the last administration.

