### 8.2. WITHDRAWAL CRITERIA AND PLANNED ANALYSIS OF WITHDRAWALS AND ABANDONMENTS

Inclusion is defined as obtaining the subject's consent to participate in the study, regardless of whether eligibility is confirmed. Patients who have been included will discontinue their participation in the clinical trial if any of the following occur:

- Presence of a serious adverse event since inclusion that, in the opinion of the investigator or sponsor, may jeopardize patient safety or affect the results of the trial.
- Abnormal laboratory value(s), whenever in the opinion of the investigator and/or sponsor the safety of the patient is at risk or may interfere with the interpretation of the results of the study.
- Poor evolution or clinical conditions of the patient that prevent its continuity.
- Indication of prohibited medications or rescue therapies in case of poor wound evolution.
- Technical difficulties in the provision of the investigational drug. In this case, the patient may be re-evaluated when adequate production is possible. The patient will keep his or her assignment number in this case.
- When the patient does not cooperate or does not meet the requirements of the study.
- Withdrawal of consent or loss of follow-up by the patient.
- Pregnancy.

The patient has the right to discontinue the study at any time and any patient may be withdrawn from the study for any reason beneficial to their well-being. If, during the study, the patient's evolution makes it advisable to apply rescue therapies with proven efficacy, the patient will automatically leave the trial, and a failure of the therapy will be recorded in the course of the study will be treated within the guideline that the clinical experts and the health authorities decide.

For the purposes of the safety objective of the trial, safety follow-up of enrolled and withdrawn patients should be ensured throughout the duration of the clinical trial (12 months), to the extent possible. In any case, the date and reason why a subject discontinues participation in the clinical trial should be recorded in the Data Collection Notebook, and the sponsor should be notified immediately if the discontinuation is due to a Serious Adverse Event.

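### Time to wound closure is right-censored, but section 11 assigns it, with every quantitative variable, to mean or median summaries and ANOVA or rank tests, with no place for an ulcer that has no closure date

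*Protocol*

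**What the plan says.** - Protocol 4.2, first secondary objective: "To determine the effect of experimental treatment on wound closure time compared to the control group". The hypothesis in section 3 also rests on shorter closure time.
- Protocol 10.2 defines the variable: "Time elapsed (days) to wound closure, measured from the start of treatment to the absence of continuity solution". An ulcer that does not close has no value under this definition.
- Protocol section 7, visit 15 onwards: "If the ulcer is not healed, a weekly safety and efficacy follow-up will be carried out until it is completely closed". The same section ends follow-up 12 months after the last administration.
- Protocol 8.2 allows exit through loss to follow-up, withdrawal of consent or poor evolution. Where rescue therapy is applied, "the patient will automatically leave the trial, and a failure of the therapy will be recorded".
- Protocol section 11 summarises quantitative variables by mean and SD or by median and quartiles. For comparing the groups it states that "for quantitative variables, the ANOVA and post hoc tests or the Kruskal-Wallis H and Mann-Whitney U tests will be used", "always applying the Bonferroni correction". It names no survival method, no censoring rule and no exception for time to closure.
- Protocol 5.3: patients "will be randomized 1:1 to two intervention arms: experimental and control (10 patients treatment group/10 patients control group"), and "no mathematical calculation of the sample size has been carried out".

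**The concern.** Time to closure is a number of days, so the general rule in section 11 applies to it as written. ANOVA and rank tests need a value for every patient, and an open ulcer supplies only a lower bound. The analyst must then improvise.

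- Analysing closed ulcers only discards the patients who did worst and compares two groups selected on the outcome.
- Entering the last follow-up day as a closure understates the times. For a patient who left early for rescue, it turns a failure into a fast closure.

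A treatment that makes more ulcers close could then show little or no difference in closure time. The handling would also be chosen after the data are known, in an open-label trial.

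**Working it through.** The protocol gives no closure rate, effect size or power, so there is no figure to reproduce. All closure rates below are assumptions.

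**Inputs from the protocol.** 10 patients per arm (5.3); weekly assessment of open ulcers (section 7); last dose on day 21, so follow-up ends at about day 21 + 365 = 386; significance at 0.05 (section 11), taken as two-sided. The Bonferroni correction is not applied, because the number of comparisons is not given.

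**1. Will there be open ulcers?** If each ulcer closes within follow-up with probability p, the chance of at least one open ulcer among 20 is 1 − p^20.
- p = 0.95: 1 − 0.95^20 = 64%.
- p = 0.90: 1 − 0.90^20 = 88%.

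**2. What closers-only times show.** Assume constant hazards with 40% (control) and 70% (treated) closed by day 84.
- Control: λ = −ln(0.6)/84 = 0.00608 per day. Treated: λ = −ln(0.3)/84 = 0.01433 per day. Hazard ratio 2.36 (about 2.4).
- Share open at day 386 is exp(−386λ): control 9.6%, treated 0.4%.
- True mean is 1/λ: control 164.4 days, treated 69.8 days, ratio 0.42.
- Mean among closers is 1/λ − T·exp(−λT)/(1 − exp(−λT)) with T = 386: control 123.6 days, treated 68.2 days, ratio 0.55.
- Mean with day 386 entered for open ulcers is (1 − exp(−λT))/λ: control 148.7 days, treated 69.5 days, ratio 0.47.

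Both substitutes pull the ratio towards 1. With a hazard ratio of 3 (true ratio 0.33), the closers-only ratio is 0.82, 0.70 or 0.54 when 40%, 60% or 80% of controls close within follow-up.

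**3. Power at the 12-month horizon.** Simulation of 10 against 10, closure times rounded up to weekly visits, everyone followed to day 386. Ranges are across independent runs of 3,000 to 5,000 trials.

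| Scenario (assumed) | Mann-Whitney, closers only | Mann-Whitney, open ulcers ranked last | Log-rank |
|---|---|---|---|
| Hazard ratio 2.4, as in step 2 | 23–24% | 32–34% | 44–45% |
| Share that ever closes 90% v 40%, same speed among closers (median 42 days) | 3–4% | 48–51% | 63–65% |

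In the second scenario the closers-only times do not differ between arms, so the whole benefit disappears from that comparison.

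**4. No treatment effect.** With 60% closing in both arms, the closers-only tests rejected in about 3% to 6% of trials. In these scenarios the harm is dilution, not false positives.

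**5. Early exits.** These were not simulated. Ranking open ulcers last works only when all patients are observed to the same day. A patient lost while open on, say, day 60 can be ranked neither last nor at day 60, whereas a log-rank test uses the 60 days and censors.

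**The case against.** - **Section 11 does not say that open ulcers are excluded.** Correct. A reader might infer that they drop out, but that is one way of applying a rule that is silent on them. Mann-Whitney, which section 11 names, can keep every patient by ranking open ulcers last. With a common end of follow-up, entering the last day gives almost the same ranks and distorts mainly the reported times. In the hazard-ratio scenario, about half of the gap between closers-only and log-rank is rank test against log-rank. What remains is that the ranking is not specified and does not handle early exits.
- **A day-84 cut would look worse.** It would: about 4% against 28–29% in the first scenario. But the 12-week limit in 10.2 belongs to the percentage healed, not to time to closure, so those figures are not used for the size.
- **The trial has other ways to see a benefit.** The 12-week healing percentage can count open ulcers as failures, and area reduction and RESVECH also use them. This stands and limits the damage, although those variables do not answer the closure-time objective.
- **A shorter time in one arm could be spurious.** A reader might infer this from selective loss of non-closers. No scenario examined produced it. Unequal early exits might, but that was not shown.
- **The endpoint is secondary.** Feasibility and safety are the main variables, there are 20 patients, and even the log-rank test has modest power. This stands and lowers the priority.
- **An analysis plan not shown may name a survival method.** It would then depart from a rule that the protocol states without exception, so the protocol text still needs correcting.

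**Conclusion.** The point holds. Sections 7, 8.2 and 10.2 make time to closure right-censored, and section 11 fixes a method for it that has no place for an ulcer without a closure date. If only closed ulcers are compared, the effect is diluted towards no difference: power of about 23% against 44% for log-rank at a hazard ratio of 2.4, and about 3% against 63–65% if treatment changes only the share that closes. Ranking open ulcers last reaches about 32% and 48%.

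These figures rest on assumed closure rates, constant hazards in the first scenario, complete follow-up to day 386 and an uncorrected two-sided 0.05. If nearly all ulcers close within 12 months, the loss from handling open ulcers shrinks. The documents support neither a claim that open ulcers will certainly be dropped nor one of inflated false positives. This is a correction that should be made before the data are analysed. It does not affect the main objectives.

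**What to change.** In section 11, except time to wound closure from the rule for quantitative variables and specify:

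- Kaplan-Meier curves by arm and a log-rank test, in all randomised patients, with time counted from day 0.
- Ulcers still open are censored at the last ulcer assessment.
- Patients already recorded as therapy failures under 8.2 stay in the analysis as not closed through the end of follow-up, and are not censored at their exit. Censoring at exit would treat them as if they had the same prospects as patients still under observation.

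No change to the withdrawal or rescue rules in 8.2 is needed for this. The weekly ulcer assessments already supply the data, so the cost is protocol wording and slightly more analysis work.
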